# Growth and safety of infants with cow’s milk allergy receiving a new hydrolyzed rice protein-based formula containing 2-fucosyllactose and lacto-N-neotetraose: protocol for a randomized clinical trial. The RIGHT-GO study

**DOI:** 10.3389/fnut.2026.1784490

**Published:** 2026-04-24

**Keywords:** children, cow’s milk allergy, growth, human milk oligosaccharides, infant formula, rice, safety

## Abstract

**Clinical trial registration:**

https://clinicaltrials.gov/study/NCT06633250, Identifier: NCT06633250.

## Introduction

1

Cow’s milk allergy (CMA) is one of the most common food allergies in childhood, with an estimated global prevalence of 0.5 to 7.5% (1–3). Clinical manifestations of CMA range from mild to severe and include cutaneous, gastrointestinal, respiratory and general symptoms (4). Breastmilk is the ideal source of nutrition for all children including for those with CMA (1). However, in situations where breastfeeding is not possible, it is essential to utilize a suitable hypoallergenic formula.

Historically, extensively hydrolyzed formulas (eHF) and amino acid-based formulas (AAF) were utilized for infants diagnosed with CMA. In the last two decades, hydrolyzed rice formula (HRF) were developed, and are now endorsed by most expert societies, such as the European Society of Pediatric Gastroenterology, Hepatology and Nutrition (ESPGHAN), as a suitable plant-based alternative to cow’s milk-derived eHF for the dietary management of CMA when breastfeeding is not possible (1). The World Allergy Organization Diagnosis and Rationale for Action against Cow’s Milk Allergy (DRACMA) and the Nutrition Committee of the French Society of Pediatrics also recommend using an extensively cow’s milk-based hydrolyzed formula or a hydrolyzed rice formula as the first option for managing non-breastfed infants with immunoglobulin E (IgE) and non-IgE-mediated CMA (2, 5). On the other hand, the Global Allergy and Asthma European Network (GA^2^LEN) Task Force makes no recommendation for or against hydrolyzed plant-based formulas for managing food allergy in infancy (6). The use of HRF has been limited by geographical availability and healthcare professionals awareness (7), but HRF are increasingly accessible today, and a growing body of evidence is being generated to support their use.

Rice is a valuable source of protein providing several essential amino acids (4). HRF are generally fortified with limiting amino acids such as lysine and threonine to fulfill the amino acid requirements of children. The protein derived from rice is hydrolyzed to enhance its water solubility (4). Rice is a cereal with low allergenicity and absence of cross-reactivity with cow’s milk proteins, making rice-based formulas an appropriate alternative for children with CMA (4, 8, 9). There have been concerns regarding the arsenic content in rice, however arsenic levels in HRF are rigorously tested and maintained within the safe range stipulated for ‘food for special medical purposes intended for infants and young children’ (FSMP) in the European Union framework (EU 2023/915 of 25 April 2023) (10, 11).

The most appealing attributes of HRF are their plant-based source and palatability. There is a growing trend towards using plant-based sources of protein in the diets of modern societies including for children. Additionally, HRF may have better palatability compared to eHF and AAF (12), offering families a broader range of options for the nutritional management of non-breastfed children with CMA. Moreover, HRF are gaining popularity among healthcare professionals due to their proven efficacy and safety, comparable to eHF, and high acceptability among consumers. Based on available evidence, rice formulas without HMOs have been shown to be safe, well tolerated and hypoallergenic in children with CMA (7). Clinical studies have shown that feeding formulas based on rice-protein hydrolysates ensures satisfactory growth from the first weeks of life up to 24 months of follow-up and supports good gastrointestinal tolerance both in healthy children (13, 14) and in those with CMA (15–22). However, HRF have been less studied than cow’s milk-based eHFs, and data from large, well-conducted randomized clinical trials is limited (1).

Human milk oligosaccharides (HMOs) are the third largest solid component of human milk but are almost absent from cow’s milk (23). HMOs are a group of a diverse and complex oligosaccharides that support gut microbiota and immune health (24), with 2-fucosyllactose (2’FL) and lacto-N-neotetraose (LNnT) being among the most abundant HMOs (25). The addition of 2’FL and LNnT to an eHF formula have partially corrected the dysbiosis commonly seen in infants with CMA (26), and importantly they were safe and associated with a lower infection rate and a lower risk of antibiotic use in children with CMA (27). Manufactured HMOs are increasingly added to infant formulas owing to their expected benefits, yet their addition to HRF remains scarce. Only one small single-arm study has investigated the growth and tolerance of a HRF containing 2’FL in 27 infants with feeding intolerance symptoms or suspected CMA and showed a good safety profile (21). To our knowledge, no study has tested the combination of a HRF with 2’FL and LNnT in children with CMA.

The purpose of this study is to determine whether a new HRF containing two manufactured HMOs (HRF-HMO) is safe and well-tolerated by infants with CMA. The primary objective is to demonstrate that infants with CMA fed the HRF-HMO have age-appropriate growth that is non-inferior to that of infants with CMA fed a control eHF with manufactured HMOs (eHF-HMO). Secondary objectives are to evaluate other growth metrics, gastrointestinal tolerance, allergy-related symptoms, health-related quality of life, and formula acceptability and palatability.

## Methods and analysis

2

### Study design and setting

2.1

The RIGHT-GO study is a randomized, blinded, non-inferiority trial with a parallel arm design. It will involve participation from 19 centers across three countries: Poland, Italy, and Germany. The study will be conducted by investigators specializing in pediatric allergy, pediatric gastroenterology, and general pediatrics in academic and private institutions. The study (Protocol version 1.0, dated 20 February 2023) was approved by ethical committees of all participating sites, and all procedures will be conducted according to the Helsinki Declaration.

The acronym ‘RIGHT-GO’ stands for ‘Rice-based Infant formula Growth and Hypoallergenicity Trials.’ This initiative encompasses two key studies: a growth and safety study, known as ‘RIGHT-GO study’ and a hypoallergenicity study referred to as ‘RIGHT-HY study’. Figures 1, 2 summarize the PICOT framework and design of the RIGHT-GO study.

**Figure 1 fig1:**
[figure not shown]
PICOT framework. CMA, cow’s milk allergy; HMO: human milk oligosaccharides; 2’FL, 2-fucosyllactose; LNnT, lacto-N-neotetraose.

**Figure 2 fig2:**
[figure not shown]
Study flow chart. CMA, cow’s milk protein allergy; EHF, extensively hydrolyzed formula; HRF, hydrolyzed rice formula.

### Selection and treatment of infants

2.2

Term, singleton infants ≤ 8 months of age who are formula-fed at the time of enrollment, and who have physician-diagnosed or suspected CMA will be eligible for enrollment. Suspected CMA is defined as per standard clinical practice and in conjunction with at least two of the following symptoms: inconsolable crying, regurgitation, liquid stools or constipation, skin atopic lesion, cow’s milk provoked temporary urticaria/angioedema or vomiting, bloody streaks in stool, or respiratory symptoms. If an infant has been diagnosed with CMA based on either a food challenge, positive IgE blood test or skin prick test, only one other symptom is required. Parents should be willing to feed their infants a cow’s milk elimination diet throughout the study.

Infants who have a history of intolerance to eHF or rice protein allergy will be excluded as well as infants with chronic medical disease (except atopic eczema), major gastrointestinal disease, known or suspected lactose intolerance or malabsorption, glucose-galactose malabsorption or soy allergy. In addition, infants with or history of severe anaphylaxis to cow’s milk or breastmilk prior to enrollment will be excluded. Infants with a weight-for-age or height-for-age z-score <−2 or >2 on the World Health Organization (WHO) Growth Standards at enrollment will also not be eligible for enrollment.

#### Sample size

2.2.1

The sample size calculation is based on the reported weight-for-age z-score after 4 months of formula feeding in a similar study in infants with CMA (27). To demonstrate non-inferiority with 90% power, a non-inferiority margin of - 0.5 z-score and *α*-level of 0.05, 36 infants would be needed per group. This calculation assumes that the control group would have growth rate that is 0.03 z-score slower than the test group due to a slightly lower protein content in the control formula. Assuming a drop-out rate of 30%, a total sample size of 104 infants (52 infants per group) will need to be recruited to have 72 completers (36 per group).

#### Randomization, allocation and blinding

2.2.2

Upon obtaining informed consent, infants will be randomized to Test or Control Formula in a 1:1 ratio. Randomization will be carried out by minimization with center, sex, and age category (0 to ≤60 days, 60 to ≤ 120 days, 120 to ≤ 180 days, > 180 days) as stratification factors, using the dynamic allocation 2nd Best algorithm provided by Medidata Rave ‘Randomization and Trial Supply Management’ (RTSM) technology. The second-best probability parameter (i.e., the probability that Rave RTSM assigns a subject to one of the second-choice study group assignments) will be set at 15% to reduce the deterministic nature of the minimization algorithm.

The identity of the products will be blinded to infants’ parents/caregivers, investigators, site personnel, the contract research organization managing the study, and the sponsor (except the manufacturing site, supply, and quality managers). The products will be packaged and labelled identically but will be distinguishable by unique codes affixed on the primary packaging. An individual coding of cartons will be used to prevent from unblinding in case of emergency unblinding. This latter may be requested by investigators in case of serious adverse events suspected to be related to the investigational product and requiring knowledge of the study product administered.

### Interventional methods

2.3

#### Test formula: HRF-HMO

2.3.1

The Test formula is a hydrolyzed rice protein-based formula, without lactose, containing two manufactured HMOs structurally identical to human milk oligosaccharides, 2’FL and LNnT, at 1.5 g/L in a 2:1 ratio. These HMO levels were chosen to be close to those found in human milk. The protein content is 2.3 g/100 kcal with a Protein Digestibility-Corrected Amino Acid Score (PDCAAS) of 1. The arsenic content of the formula is maintained within safe limits, below the maximum inorganic arsenic content for FSMP intended for infants and young children under the age of 3 set by the European commission (Regulation EU 2023/915 of 25 April 2023) (28). The macronutrient and HMO composition of the study formulas is presented in Table 1.

**Table 1 tab1:** Macronutrient and HMO composition of study formulas.

Formula composition	Hydrolyzed rice protein-based formula (HRF-HMO)	Extensively hydrolyzed whey-based formula (eHF-HMO)
Caloric density (kcal/100 mL)	67.5	66.5
Protein (g/100 kcal)	2.3*	2.20
Protein (g/100 mL)	1.55	1.46
Protein source	Hydrolyzed rice protein	Extensively hydrolyzed whey
Lipids (g/100 kcal)	5.2	5.2
Carbohydrate (g/100 kcal)	10.8	11.1
Carbohydrate source	Maltodextrin, starch	Maltodextrin, lactose
2’FL (g/L)	1.0	1.0
LNnT (g/L)	0.5	0.5

EHF, extensively hydrolyzed formula; HRF, hydrolyzed rice formula; HMO, human milk oligosaccharides; 2’FL, 2-fucosyllactose; LNnT, lacto-N-neotetraose.*minimum protein value of 2.25 g/100 Kcal.

#### Control group: eHF-HMO

2.3.2

The control formula is a commercially available extensively hydrolyzed whey-based formula (Althéra® HMO, Nestlé Health Science, Vevey, Switzerland) with lactose, containing the same type and amount of HMOs as the Test formula. The protein content of the Control formula is 2.2 g/100 kcal. This formula was selected as a control as eHF are the standard of care for non-breastfed infants with CMA. Furthermore, this formula contains the same HMOs as the test formula.

The Test and Control formulas are both considered ‘FSMPs’ intended for infants with CMA. Both formulas are nutritionally complete FSMPs and fall in the scope of Delegated Regulation (EU) 2016/128. The formulas will be provided in powder form and administered orally after reconstitution with water, using an infant feeding bottle, cup, bowl, or other container depending on age and developmental stage. Instructions for proper study formula handling and preparation will be provided to parents. Minor taste differences exist between the two formulas due to their inherent composition.

Study formulas will be administered for 4 months, and infants will be fed daily *ad libitum.* The volume of formula required each day may vary depending on the infant’s age, weight, and appetite. After 4 months of feeding the assigned study formula, parents will be offered post-study access to their assigned formula until the child is 12 months of age. This continued access to the study formula is intended to ensure the health and well-being of all study participants who may still need access to a hypoallergenic formula that has been identified as beneficial for that participant during the study.

### Data analysis

2.4

#### Primary outcome

2.4.1

The primary outcome is weight-for-age z-score after 4 months of intervention. The treatment difference between the Test formula and Control formula will be estimated by a linear mixed-effect model. Fixed effects will include baseline weight-for-age z-score, age at baseline (0 to ≤ 60 days, 60 to ≤ 120 days, 120 to ≤ 180 days, > 180 days) and center. Random effect will be the infant. Primary analysis will be in the per-protocol (PP) dataset. Weight-for-age z-score after 4 months of test formula intake will be at least as good as the control, if the treatment difference between the Test group (HRF-HMO) and Control group (eHF-HMO) is < −0.5 SD (non-inferiority margin) (29). The treatment difference is superior to −0.5 SD if the lower bound of the two-sided 95% confidence interval is more than −0.5 SD. Such procedure corresponds to a one-sided testing at 2.5% level.

#### Secondary outcomes

2.4.2

##### Growth assessment

2.4.2.1

Growth outcomes include weight-for-age, length-for-age, head circumference-for-age, weight-for-length and BMI-for-age z-scores, as well as tibia and femur length. Weight and length will be collected at enrollment and monthly throughout the study, while head circumference, tibia and femur length will be measured at baseline and at 4 months post-intervention. Anthropometry parameters will be measured using standardized methodology and calibrated instruments by trained personnel. Weight, length and head circumference measurements will be performed two times by two trained persons, to the nearest 10 g, 0.1 cm and 0.1 cm respectively; they will then be plotted against the WHO Growth Standards. Tibia length corresponds to the distance between the tip of the medial condyle and the tip of the medial malleolus. Femur length is the distance between the tip of the greater trochanter and the lowest point of the lateral condyles. Both measurements should be taken three consecutive times, to the nearest 0.1 cm in a lying position using a tape measure.

Considering that complementary food intake may affect growth outcomes, dietary intake will be evaluated through 24-h dietary recalls conducted at baseline, as well as at the 2 and 4-month visits. This assessment aims to determine the type and quantities of all foods and beverages consumed by the infant. Investigators will receive detailed instructions and training to ensure accurate recording of complementary food intake.

##### Gastrointestinal tolerance

2.4.2.2

To assess gastrointestinal (GI) tolerance to study formulas, the Infant Gastrointestinal Symptom Questionnaire (IGSQ) will be administered at each visit and via a phone call after the first week of study formula use. IGSQ is a validated questionnaire including 5 symptom clusters, yielding a 13-item index of parent-reported infant digestion and elimination behaviors over the prior 7 days (30). It is the most commonly used tool to assess infant GI-related symptoms in clinical studies. During the first week of the study period, a daily gastrointestinal tolerance questionnaire will also be completed by the parents, including questions on the presence and severity of flatulence, vomiting, crying, fussing and sleep duration.

The Brussels Infant and Toddler Stool Scale, a validated stool scale, will be used to assess stool consistency (31). Parents will document stool frequency and consistency (categorized as watery, loose, formed, or hard) in a diary over three consecutive days prior to the 2- and 4-month visits, along with a one-day retrospective record of stool frequency and consistency at baseline.

##### Allergy symptoms

2.4.2.3

Assessment of allergy symptoms will be conducted at baseline and each visit using the Cow’s Milk-related Symptom Score (CoMiSS) (32). CoMiSS is a validated awareness tool for CMA and includes possible manifestations of CMA such as skin, GI, respiratory and general symptoms. CoMiSS can also be used to evaluate and quantify the evolution of allergy symptoms, with scores ranging from 0 to 33.

##### Health-related quality of life assessment

2.4.2.4

Health-related quality of life assessment will be measured at baseline and at the 4-month visit using validated questionnaires. Parental quality of life will be assessed using the Food Allergy Quality of Life Questionnaire, parent form (FAQLQ-PF) (33), and parental self-efficacy in managing child’s food allergy will be evaluated using the Food Allergy Self-Efficacy Scale for Parents (FASE-P) (34). Parent-reported infant health-related quality of life will be measured using the Infant and Toddler Quality of Life Questionnaire-Short Form (ITQOL-SF47) (35).

##### Formula compliance and liking

2.4.2.5

Compliance to study formulas will be monitored during each visit through a standardized set of questions inquiring about the volume of formula intake, any interruptions to the study formula, as well as the consumption of unauthorized formulas or complementary foods, particularly in relation to adherence to the cow’s milk elimination diet. Compliance is also verified via formula accountability at each visit by counting the number of remaining and returned cans. A ‘non-compliant day’ is defined as any day on which a formula other than the study formula was consumed, complementary foods or drinks containing cow’s milk products were ingested, or complementary feedings were introduced prior to the age of four months. A compliance threshold of 85% was established to define adequate adherence to study products. Formula liking will be assessed at the end of the study via a simple questionnaire that captures the ease of formula preparation and overall liking by the parent and child.

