#### Data analysis

2.4.4

The analyses of this study will adhere to the recommended guidelines outlined in the CONSORT 2022 statement for reporting outcomes in clinical trial reports (36).

The Intention-to-Treat (ITT) analysis population will include all randomized infants. The full analysis set (FAS) will consist of a subset of subjects from the ITT with available weight-for-age z-scores at baseline and 4 months and available measurements for all other covariates included in the model. The Per Protocol (PP) set will include all infants from the FAS having no protocol deviations impacting the primary endpoint, nor documented concomitant medication intakes impacting the primary endpoint, nor violated eligibility criteria. In particular, infants that are non-compliant to feeding interventions will be excluded from the PP set. The analysis in aforementioned populations will be conducted using the assigned intervention. The safety analysis set (SAF) will consist of all infants in the ITT population with documentation of at least one administration of study product, analyzed according to the product received irrespective of the randomization assignment. The primary and secondary endpoints will be analyzed in both FAS and PP populations.

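### The non-compliant-day definition does not count days without study formula, so the 85% threshold measures avoidance of other products, and largely unexposed infants can remain in the primary per-protocol set

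*Protocol article*

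**What the plan says.** All references are to the protocol article.

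- **Section 2.4.2.5 (Formula compliance and liking)** gives three triggers for a non-compliant day. The first "is defined as any day on which a formula other than the study formula was consumed". The second is that "complementary foods or drinks containing cow’s milk products were ingested". The third is that "complementary feedings were introduced prior to the age of four months".
- The same section then states: "A compliance threshold of 85% was established to define adequate adherence to study products".
- It also describes exposure data. Parents are asked questions "inquiring about the volume of formula intake, any interruptions to the study formula", and "Compliance is also verified via formula accountability at each visit by counting the number of remaining and returned cans".
- **Section 2.4.4 (Data analysis)** builds the per-protocol (PP) set from the full analysis set (FAS) by removing infants with deviations or concomitant medication affecting the primary endpoint, or with eligibility violations. It adds, as a particular case, that "infants that are non-compliant to feeding interventions will be excluded from the PP set".
- **Section 2.4.1 (Primary outcome)** makes the PP set the primary analysis set. Section 2.4.4 has the endpoints analysed in the FAS as well.
- **Section 2.2 (Selection and treatment of infants)** admits "infants ≤ 8 months of age who are formula-fed at the time of enrollment". It does not say that formula feeding must be exclusive.
- **Section 2.3.2** plans four months of daily study formula, taken ad libitum.

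**The concern.** The threshold is presented as a measure of adherence to the study products, but every trigger beneath it concerns something else the infant was given. None asks whether study formula was taken. A day on breast milk, or on dairy-free solids after four months of age, with no study formula at all, meets none of the three triggers and scores as compliant.

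This reaches the primary analysis. Section 2.4.2.5 holds the only operational definition of compliance in the article, and section 2.4.4 excludes infants from the PP set for non-compliance. In a non-inferiority trial the PP set is made primary because it should reflect actual exposure to the two products. Infants with little exposure tend to pull the arms together, and that helps the test product pass the margin.

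The situation is possible in this population. An infant enrolled at 8 months finishes at about 12 months, when solids can be a large part of the diet. Section 2.3.2 acknowledges minor taste differences between the formulas.

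**Working it through.** **1. The rule applied to two infants.** The article does not give the denominator of the 85%. Assume it is days in the study, about 4 × 30.5 = 122.

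| Infant (older than four months throughout) | Non-compliant days | Compliance |
|---|---|---|
| A: study formula daily, but another formula also given on 19 days | 19 | 103/122 = 84.4%, fails |
| B: no study formula after week 1, only breast milk and dairy-free solids | 0 | 122/122 = 100%, passes |

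The threshold tolerates 18 days with a trigger (104/122 = 85.2%). On the literal wording it puts no limit on days without study formula.

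**2. The plan's own figures.** Section 2.2.1 gives 36 per group, 90% power, a margin of −0.5, an assumed difference of +0.03 in favour of the test formula, and 30% drop-out.

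- Drop-out: 36/0.70 = 51.4, rounded up to 52 per group and 104 in total. This reproduces.
- The 36 cannot be checked forward, because no SD is given. Solving backward at one-sided 2.5%, the level in sections 2.4.1 and 2.4.4: SD = (0.5 + 0.03) × √(36/2) / (1.960 + 1.282) = 0.53 × 4.243 / 3.242 ≈ 0.69.
- If the 0.05 in section 2.2.1 were one-sided, the same step would give about 0.77. Because of rounding up in the sample size, 0.765 is used below as the second value.

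**3. Illustrative dilution.** Assumptions that are not in the documents:

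- a fraction f of the PP set in each arm is effectively unexposed;
- those infants grow alike in both arms;
- the true difference in exposed infants lies exactly at the margin, −0.5;
- the PP set has 36 per arm.

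Expected difference: d = −0.5 × (1 − f).

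SE = SD × √(2/36), which is 0.163 for SD 0.69 and 0.180 for SD 0.765.

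P(non-inferiority concluded) = Φ((d + 0.5)/SE − 1.96).

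Example at f = 10%, SD 0.69: d = −0.45, and Φ(0.05/0.1626 − 1.96) = Φ(−1.65) = 4.9%.

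| f | d | SD 0.69 | SD 0.765 |
|---|---|---|---|
| 0% | −0.500 | 2.5% | 2.5% |
| 2% | −0.490 | 2.9% | 2.8% |
| 5% | −0.475 | 3.5% | 3.4% |
| 10% | −0.450 | 4.9% | 4.6% |
| 20% | −0.400 | 8.9% | 8.0% |

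With 36 per arm, 5% is about 2 infants per arm and 10% about 4. Power at the planned +0.03 hardly moves: 90.3% at f = 0 and about 89.7% at f = 20% (SD 0.69).

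**4. The FAS as a safeguard.** The PP set is a subset of the FAS, so every unexposed infant left in the PP set is in the FAS too. Agreement between the two analyses would not reveal this dilution.

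**The case against.** **The PP set has a wider rule.** Non-compliance is only a particular case of excluding deviations that affect the primary endpoint, and section 2.4.4 does not say the 85% is the sole compliance test. An infant who stopped the study formula could be removed under the wider rule. This stands, and it means retention is not certain. But that rule sets no criterion for intake. With ad libitum feeding, a day of little or no formula is not plainly a deviation, so removal would rest on judgement while the numeric rule scores the infant as compliant.

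**The article is condensed.** How volume, interruptions and can counts are combined with the 85% may be set out in the full protocol or analysis plan. That is a fair reason not to object to a missing detail. Here, however, a definition is stated in full, and as stated it misclassifies.

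**The gap is narrow.** Infants are formula-fed at entry. Most who refuse the study formula would be given another, which the first trigger catches, and early solids are caught by the third. What remains is breast milk, or dairy-free food after four months. This stands, and it argues for a small affected fraction.

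**The direction is assumed.** If unexposed infants grow worse and are more common in one arm, the shift could go either way. This stands: the direction toward zero holds only if they grow alike and occur equally in both arms.

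**The fix conditions on a post-randomization event.** Refusal may differ by arm. This also stands, but the PP set is already conditioned on adherence. It bears mainly on any further restriction by amount of intake.

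**Conclusion.** The definition should be corrected. As written it leaves out the one event most directly tied to adherence, a day without study formula, although the data to identify such days are collected. Infants who largely stopped the formula can therefore count as adherent, and can remain in the primary analysis unless judgement removes them.

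A reader might infer that unexposed infants will stay in the PP set and that the primary result is biased toward non-inferiority. The documents do not support that. The wider deviation rule may remove such infants, the article gives no count of them, and nothing is known about their growth. Nor do the documents support large affected fractions.

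Under the stated assumptions (SD about 0.69, true difference −0.5, 36 per arm, unexposed infants growing alike and equally common in both arms), false non-inferiority is about 3.5% at 5% unexposed and about 5% at 10%, against 2.5% with none. The effect is modest unless roughly a tenth or more of the PP set is unexposed. Infants with only some days off formula are partly exposed and would dilute less.

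**What to change.** - Add a fourth trigger to the definition in section 2.4.2.5: *or any day on which no study formula was consumed*.
- Count these days against the 85%, using the interruption and volume questions and the can accountability already planned.
- State what the 85% is a percentage of, for example days from randomization to the 4-month visit.
- Make these changes before unblinding, so that PP membership does not depend on case-by-case judgement about exposure.

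A sensitivity analysis restricted by recorded intake is optional. Any cut-off should be fixed before unblinding, and the result read with caution, because intake arises after randomization and may differ by arm. No cut-off is proposed here.

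The cost is the wording of one definition, with no new data collection. The downside is that a few more infants may leave the PP set, with a small loss of precision. Reporting exclusions for this reason by arm would show whether they are balanced.
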